### Study design

We will conduct a hybrid type 3 implementation-effectiveness cluster-randomized trial design [25] to investigate mobile-based supervision of YRI delivery by teachers in Sierra Leone’s secondary schools as a new implementation strategy, with clinical outcomes of the YRI on youth mental and behavioral health as secondary outcomes. We will use a mixed methods approach to investigate study aims. The Exploration, Preparation, Implementation, Sustainment (EPIS) framework [26], a broad, context sensitive implementation science process model, will guide study implementation. Randomization to study condition will occur at the level of the school. Schools (*n* = 50) will be randomized to YRI with mobile-based supervision (*n* = 20 schools/*n* = 480 youth), YRI with standard (in-person) supervision (*n* = 20 schools/*n* = 480 youth) or control (*n* = 10 schools/*n* = 240 youth). Control schools are necessary primarily for the cost-effectiveness analysis because they will provide reference level estimates of QALYs gained by intervention schools. We selected an unequal randomization design to reduce the number of youths who are exposed to the waitlist control [27]. We will offer YRI training to interested teachers in control schools following 12-month follow-up data collection. To optimize comparability between schools, we will match schools into quintets using an algorithm prior to randomly assigning two members of each quintet to each supervision model and the fifth to the control. All research assistants and data analysts will be blinded to participant assignment and will assign schools to study condition based on the allocation sequence.

Regarding standard reporting, this study will adhere to the Standard Protocol Items: Recommendations for Intervention Trials (SPIRIT) guidelines (See Fig. 2) and the Consolidated Standards of Reporting Trials (CONSORT). This trial is registered with the Clinical Trials Registry maintained by the National Library of Medicine at the National Institute of Health (Trial ID: NCT05737667; registered on 02/02/23). This study is approved by the Brown University Institutional Review Board (Protocol #2,022,003,442) and the Sierra Leone Ethics and Scientific Review Committee. Any subsequent modifications will be reviewed by both of these review committees for approval and then submitted to the Clinical Trials Registry as an amendment. The study protocol was also eviewed as part of the funding application.

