We will recruit 480 youth from the 40 secondary schools randomized to receive the YRI delivered with mobile supervision and 480 youth from schools that will receive YRI delivered with standard supervision. We will enroll 240 youth from 10 control schools. We will aim to recruit 24 youth per school, with two YRI groups per intervention school. We aim to recruit an equal number of male and female participants, as the YRI is delivered in separate groups for males and females. The target sample size of 1200 youth is powered to account for 10–20% attrition per our prior experience in Sierra Leone. Youth inclusion criteria are: (a) currently enrolled in a secondary school in the Western region; (b) male or female aged 14–24; (c) able and willing to attend an extracurricular school activity. Parental consent and youth assent will be obtained for all youth under age 18.

Our target age for enrollment of youth (aged 14–24) is based on prior research on the YRI demonstrating that the intervention is effective with male and female populations within this age range [19, 20]. Including students 18–24 reduces potential bias towards those youth who take longer to complete secondary school, delayed entry into school, or dropped out of school and later returned. Excluding students older than age 24 ensures we are targeting the developmental window of youth as defined by the United Nations and the World Health Organization.

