### Data analysis

#### Quantitative analysis

We will compare fidelity trajectories of teachers receiving mobile supervision to those of teachers receiving standard supervision and investigate the null hypothesis that mobile supervision will not differ from standard supervision. We will conduct exploratory analyses to uncover typical trajectories for each supervision method (mobile-based or standard) and undertake comparisons using growth curve modeling by means of multilevel models [44]. We will use HLM software (v.8.2), which estimates multiple imputations based on the dependencies of multilevel data. Missing time points are addressed by the multilevel approach to growth modeling, and data from all enrolled participants can be analyzed in accordance with our intention to treat design. The null hypothesis is that the outcomes for the mobile supervision YRI groups will not differ from those in standard supervision YRI groups. With this approach, we can compare both YRI models (as identified by dummy variables) to the untreated control group or assess the null hypothesis of no difference between the fidelity in the two models (mobile-based vs. standard supervision).

We will also investigate the null hypothesis that mobile supervision will not differ from standard supervision at post-intervention in youth outcomes. To investigate YRI effects on mental health among youth at post-intervention, we will use multilevel models to accommodate the clustering of students within YRI groups. For analysis of student outcomes, student characteristics will be modeled in a level-one equation. The group characteristics will be modeled in the level-two equation. School characteristics will be incorporated into a third level.

However, we do not expect a significant school-level intraclass correlation (ICC) for targeted YRI outcomes. In the event we do not find a significant ICC, sector and rural/urban will be represented in the group-level equation, and a two-level model will be estimated.

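### The youth-outcome model drops the school, the unit of randomisation, if its ICC is not significant; the test is weak, its failure is expected, and control youth then have no stated cluster level

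*Protocol article*

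**What the plan says.** Under Study design, the protocol article states: "Randomization to study condition will occur at the level of the school". Twenty schools go to each supervision arm and ten to control.

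Under Quantitative analysis, the stated purpose of the youth-outcome model is clustering by group: "we will use multilevel models to accommodate the clustering of students within YRI groups". Students are level one and YRI groups level two, and "School characteristics will be incorporated into a third level". The next paragraph qualifies this: "However, we do not expect a significant school-level intraclass correlation (ICC) for targeted YRI outcomes". The consequence follows: "In the event we do not find a significant ICC, sector and rural/urban will be represented in the group-level equation, and a two-level model" takes the place of the three-level one.

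Under Settings and participants, the group structure is given for the intervention arms: "We will aim to recruit 24 youth per school, with two YRI groups per intervention school". For the third arm it says only: "We will enroll 240 youth from 10 control schools".

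**The concern.** The fallback removes the random effect of the unit that was randomised. Sector and rural/urban are fixed covariates and do not replace it. The two groups of one school are then treated as independent, and the test of arm moves from schools to groups. The decision rests on a non-significant variance component, which is weak evidence of absence with 40 or 50 schools. Because the protocol expects that result, the two-level model is the anticipated final one.

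If school variance is present, standard errors are too small and degrees of freedom too large, so the one-sided noninferiority and superiority tests on youth outcomes reject too often. A second gap concerns the control arm. Level two of the fallback is the YRI group, and the article describes no such groups in control schools, although it plans comparisons of the YRI arms with control.

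**Working it through.** **Inputs.** 20, 20 and 10 schools; 480, 480 and 240 youth; 24 youth per school and two groups per intervention school, so about 12 per group; ICC 0.03 (prior range 0.01–0.04), one-sided alpha 0.05 and power 0.8, from the power section for student outcomes. Assumptions, because the article does not give them: the test of the school ICC is an F test at 0.05, and the total ICC splits between school (ρs) and group (ρg) as shown in the table.

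**1. The protocol's own power figures.** MDES = (1.645 + 0.842) × √[DE × (1/n1 + 1/n2)], with DE = 1 + (m − 1) × 0.03.

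| Comparison | Stated | School cluster, m = 24, DE 1.69 | Group cluster, m = 12, DE 1.33 |
|---|---|---|---|
| Mobile v standard (480 v 480) | 0.21 | 0.209 | 0.185 |
| One YRI arm v control (480 v 240) | 0.26 | 0.256 | 0.227 |
| Both YRI arms v control (960 v 240) | 0.21 | 0.233 | 0.207 |

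The first two figures reproduce only with school-sized clusters, although the text attaches the ICC to the group. They therefore allow for clustering that the fallback would discard. The third fits only group-sized clusters.

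**2. How weak the trigger is.** With a balanced design, the expected mean squares are:
- schools: 24 × [ρs + (ρg + (1 − ρs − ρg)/12)/2]
- groups within schools: 12 × [ρg + (1 − ρs − ρg)/12]

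At ρs = 0.03 and ρg = 0 these are 1.69 and 0.97, a ratio of only 1.74. On 38 and 40 df (two arms, 40 schools) the F test misses this in about 47% of trials. With all 50 schools, and control schools also split in two for the test, it misses it in about 39%.

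**3. Error for mobile v standard once the school is dropped.** At the same setting the pooled mean square is (38 × 1.69 + 40 × 0.97)/78 = 1.32, against a true 1.69. The standard error is too small by a factor √(1.69/1.32) = 1.13, and 1 − Φ(1.645/1.13) is about 7.3%. That is the error if the two-level model were always used.

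Simulating the full rule from these mean squares (drop the school if F is non-significant, otherwise keep it) gives, at nominal 5% one-sided:

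| ρs + ρg | Non-significant | Two-level always | Given school dropped | Whole rule | School always kept |
|---|---|---|---|---|---|
| 0 + 0.03 | 95% | 5.0% | 5.0% | 4.9% | 5.0% |
| 0.01 + 0.02 | 85–86% | 5.8% | 5.8% | 5.4% | 5.0% |
| 0.02 + 0.01 | 65–70% | 6.5% | 6.7% | 5.7% | 5.0% |
| 0.03 + 0 | 39–47% | 7.3% | 7.6% | 5.5–5.7% | 5.0% |
| 0.04 + 0 | 23–31% | 7.8% | 8.4% | 5.4–5.5% | 5.0% |

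Two-sided, the whole rule gives 5.6–6.1% over school ICC 0.01–0.04.

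**4. One YRI arm v control in the two-level model.** The true variance at ICC 0.03, all of it at school level, is 1.69 × (1/480 + 1/240) = 0.01056. The modelled variance depends on how control youth are nested, which is not stated:
- independent: 1.33/480 + 1/240 = 0.00694, ratio 1.52, one-sided error about 9.1%
- pseudo-groups of 12: 1.33 × (1/480 + 1/240) = 0.00831, ratio 1.27, about 7.2%
- school as their level two: 1.33/480 + 1.69/240 = 0.00981, ratio 1.08, about 5.6%

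For the independent case, errors at ICC 0.01, 0.02, 0.03 and 0.04 are about 6.5%, 7.9%, 9.1% and 10.2%.

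**The case against.** The fallback does not ignore clustering as such. It keeps the YRI-group level and adjusts for sector and rural/urban, which could absorb some school variance; the calculation leaves out both those covariates and the quintet matching. The two-level model is used only after a non-significant test, so the fair summary for mobile versus standard is the whole-rule error, at most about 0.7 percentage points above nominal one-sided. The power section attaches the 0.03 to the group; if all of it sits there, nothing is inflated. Power to detect the school ICC is not poor throughout: about 53–61% at 0.03 and 69–77% at 0.04. All of this stands, and it limits the size of the problem. It does not justify the rule, because the test does not protect the analysis that follows it: given that the school was dropped, error is no lower than if the two-level model had always been used.

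A reader might infer that control youth will be analysed as independent. The article does not say so. It leaves their nesting open, and does so in the three-level model too, so the fallback does not create that gap. What it does is remove the school, the one cluster level that control youth clearly have.

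A reader might also extend the rule to the fidelity trajectories. The sentence follows the description of the student-outcome model and does not mention fidelity, so that extension is not supported.

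**Conclusion.** The point holds as a should-fix. The protocol fixes a rule that removes the randomised unit from the youth-outcome model on a weak test whose failure it expects. For mobile versus standard the cost is modest: about 5.4–5.7% one-sided over the whole rule, and about 5.8–8.4% in trials where the school has been dropped, for school ICCs of 0.01–0.04. It is nil if the school ICC is zero. For one YRI arm versus control it could be larger, about 6.5–10% one-sided, but only if control youth were treated as independent in the two-level model.

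These figures rest on a balanced design, an F test at 0.05 and an assumed split of the ICC between school and group, none of which the article specifies in full. Reading the rule as ignoring all clustering, or taking the 7–10% figures as the error of the plan as a whole, would go beyond the text. The outcomes concerned are secondary in this hybrid type 3 trial, which also keeps the grade below must-fix.

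**What to change.** Delete the fallback sentence. In every youth-outcome comparison between arms, keep a random intercept for school whatever its estimate or p-value, with small-sample degrees of freedom based on schools. Nest YRI group within school in the intervention arms only, and say that the school is the cluster level for control youth. Enter sector and rural/urban at the school level.

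The cost is a sentence or two of analysis wording and slightly wider intervals if the school variance is truly zero (38 rather than 78 degrees of freedom for mobile versus standard). With the school always kept, simulated error stays at the nominal 5% at every ICC split tried. The article reports that data collection had not started, so at that stage the change could be made without sight of any outcome.

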#### Statistical power analysis for fidelity to YRI implementation

To assess the minimal detectable effect size for the two-tailed null hypothesis of no difference for fidelity of groups receiving mobile versus standard supervision requires an estimate of the within-group ICC for fidelity for which there is no clear guidance in the literature. Given our standard assumptions, at a small to medium ICC of 0.2 for a two-tailed test with a null hypothesis of no difference for 80 groups and 12 fidelity ratings, the minimum detectable effect size would be 0.30, while at a large ICC of 0.5 the minimum detectable effect size would be 0.41.

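### The two-tailed minimum detectable effects for fidelity (0.30 and 0.41) do not follow from the stated inputs, which give 0.32 and 0.46

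*Protocol article*

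**What the plan says.** The protocol article, under Statistical power analysis for fidelity to YRI implementation, calls the comparison two-tailed twice. It introduces the figures with "Given our standard assumptions", and does not list those assumptions there. It then gives two scenarios:

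- "at a small to medium ICC of 0.2": the effect comes from a "two-tailed test with a null hypothesis of no difference for 80 groups and 12 fidelity ratings, the minimum detectable effect size would be 0.30".
- The second scenario reads "while at a large ICC of 0.5 the minimum detectable effect size would be 0.41".

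The section names no alpha, power or covariate, and has no term for the school. Under Study design the article says "Randomization to study condition will occur at the level of the school", with schools matched in quintets beforehand. Settings and participants describes recruitment "with two YRI groups per intervention school", so 40 intervention schools give the 80 groups, 40 per supervision arm.

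**The concern.** Fidelity belongs to the first study aim of a hybrid type 3 trial, and this is the article's only power statement for an implementation outcome. The hypothesis is that fidelity will be comparable between the arms. If the sensitivity is overstated, a non-significant difference will look more reassuring than it should.

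Both printed effects are smaller than a standard two-level calculation gives on the same inputs. The calculation also treats the 80 groups as independent, although they sit in pairs inside the randomised units.

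**Working it through.** **Inputs**

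- From the fidelity power section: J = 80 groups (40 per arm), m = 12 ratings per group, two-tailed test, ICC 0.2 or 0.5.
- Assumed: alpha 0.05 and power 0.80. The fidelity section does not state them; they come from the student-outcome power section, where the test is one-tailed.
- Assumed: covariate R-squared of zero, because none is stated.

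**Formula**

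MDE = (z for alpha + z for power) × SE, with SE = sqrt(4 × [ICC + (1 − ICC)/m] / J).

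- ICC 0.2: SE = sqrt(4 × (0.2 + 0.8/12)/80) = sqrt(0.01333) = 0.1155
- ICC 0.5: SE = sqrt(4 × (0.5 + 0.5/12)/80) = sqrt(0.02708) = 0.1646

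**Attempt to reproduce the stated figures**

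| Calculation | ICC 0.2 | ICC 0.5 |
|---|---|---|
| Stated, two-tailed | 0.30 | 0.41 |
| Two-tailed, (1.960 + 0.842) × SE | 0.323 | 0.461 |
| Two-tailed, t multipliers, 78 df | 0.328 | 0.467 |
| One-tailed, (1.645 + 0.842) × SE | 0.287 | 0.409 |
| One-tailed, t multipliers, 78 df | 0.290 | 0.413 |
| Two-tailed, group-level R-squared 0.22 | 0.296 | 0.412 |

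The last row replaces ICC by ICC × (1 − 0.22) in the SE.

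**Two-tailed power at the stated effects**

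- 0.30/0.1155 − 1.960 = 0.638, so power is 74%.
- 0.41/0.1646 − 1.960 = 0.531, so power is 70%.

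**Does the result hang on the assumed alpha and power?** With no covariate and 12 ratings, the multiplier cancels from the ratio of the two effects: sqrt(0.5417/0.2667) = 1.43. The printed ratio is 0.41/0.30 = 1.37, and at most 0.415/0.295 = 1.41 allowing for rounding. So no choice of alpha, power or sidedness alone yields both figures. This holds only without a covariate: with a group-level R-squared of 0.22 the ratio is 0.412/0.296 = 1.39, which rounding allows.

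**School level**

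Let s be the share of the group-level correlation that lies between schools. The documents give no value, so s is an assumption. With 20 schools, 40 groups and 480 ratings per arm:

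variance of the difference = 2 × [s × ICC/20 + (1 − s) × ICC/40 + (1 − ICC)/480], and MDE = 2.802 × its square root.

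| School share s | ICC 0.2 | ICC 0.5 |
|---|---|---|
| 0% | 0.323 | 0.461 |
| 10% | 0.335 | 0.482 |
| 50% | 0.379 | 0.557 |
| 100% | 0.428 | 0.639 |

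**The case against.** The strongest defence is that the article leaves its standard assumptions unlisted, and a covariate may be among them. A group-level R-squared of about 0.22 reproduces both figures, two-tailed, at 80% power. Adjustment would fit the design: schools are matched, and sector and urban/rural location can enter the group-level equation of the student model. This part of the objection stands, and it limits how surely the figures can be called wrong. It does not rescue the text as written, because no covariate is stated. Nor does the student-outcome section point to one: its 0.21 for mobile versus standard and its 0.26 for 20 versus 10 schools come out one-tailed, with ICC 0.03, 24 youth per school and no covariate, as 0.209 and 0.256. That support is incomplete, since the 0.21 for 40 versus 10 schools comes out as 0.233 on that basis and as 0.207 only with groups of 12.

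A reader might infer that the authors ran a one-tailed test and mislabelled it, since 0.41 is the one-tailed value. The documents do not establish this: one-tailed, the ICC 0.2 figure is 0.29, not 0.30. A one-tailed calculation with 9 ratings would give 0.299 and 0.414, but the section says 12.

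A reader might also infer that the detectable effects must rise once schools are counted. They rise only if fidelity varies between schools. No school-level ICC for fidelity is given, and quintet matching could offset part of any rise. The 100% share is an extreme, as it leaves the two groups in a school with no variation of their own. The expectation of no significant school-level ICC, under Quantitative analysis, appears with the student-outcome model and does not settle the matter for fidelity.

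Finally, the gap is modest next to the uncertainty about the ICC itself, for which the section acknowledges it has no firm basis. That is fair, and it bears on how much the error matters.

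**Conclusion.** As written, the two-tailed figures of 0.30 and 0.41 are not supported by their inputs. Without a covariate, and with alpha 0.05 and power 0.80 assumed, they are 0.32 and 0.46. The understatement is about 0.02 and 0.05 standard deviations, and power at the stated effects is about 74% and 70%. The source of the discrepancy is open: one-tailed testing explains one figure, an unstated R-squared explains both.

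The school-level range (0.32 to 0.43 and 0.46 to 0.64) is a sensitivity analysis over an assumed share, not a correction.

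It would go too far to say that 0.30 or 0.41 will serve as the threshold for calling the arms comparable. The article does not use them as a margin.

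**What to change.** - Restate the two-tailed minimum detectable effects as 0.32 (ICC 0.2) and 0.46 (ICC 0.5). If a covariate R-squared was used, keep the figures that follow from it, and state and justify that R-squared.
- In either case, state alpha, power and sidedness in the fidelity section itself.
- Add a sensitivity range for an assumed school share of the group-level correlation from 0% to 100%: 0.32 to 0.43 at ICC 0.2 and 0.46 to 0.64 at ICC 0.5. Note that quintet matching may offset part of the rise.

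The cost is a few lines of text. No more schools are needed. The drawback is that the stated sensitivity becomes less favourable.

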#### Statistical power analysis for student outcomes

Power will be sufficient to assess our secondary aim and examine the hypothesis that the YRI delivered by teachers participating in mobile supervision will be noninferior in terms of youth mental health outcomes compared to the YRI delivered by teachers receiving standard supervision. At a power of 0.8 and an alpha of *p* <.05 (one-tailed to assess noninferiority), using an ICC of 0.03 (based on prior ICCs for mental health outcomes of 0.01-0.04) [18] for the group for comparisons at a single time point (post-intervention or 12-month follow-up) for student outcomes, the minimal detectable standardized effect size for a standardized difference (d) between the two of 0.21; in other words, at a negative difference of 0.21 or smaller, mobile supervision will be considered noninferior to standard. To test individual null hypotheses that either YRI implementation model (20 schools per YRI supervision mode) is superior (one-tailed) to the 10 untreated control schools with regard to mental health or educational outcomes, we have 0.8 power to detect a standardized effect of 0.26. In a comparison of all 40 YRI schools as compared to the 10 control schools, the minimum detectable effect would be 0.21.

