#### Youth mental health outcomes

The Difficulties in Emotion Regulation Scale (DERS), will assess emotion regulation skills [37]. The DERS is a 36-item scale scored on a 5-point Likert scale, with higher scores reflecting greater difficulties regulating emotions (α = 0.91). The Hopkins Symptom Checklist (HSCL) will measure symptoms of anxiety and depression [38, 39]. The HSCL-25 consists of ten items scored on a 4-point Likert scale for anxiety symptoms (α = 0.82) and 15 for depression symptoms (α = 0.82), with higher scores reflecting worse functioning. The Adapted Youth Risk Behavior Survey is a 14-item scale adapted from the original 89-item scale that will assess priority health risk behaviors among youth (i.e., behaviors that contribute to unintentional injuries and violence, tobacco use, alcohol and other drug use, sexual behaviors that contribute to unintentional pregnancy and sexually transmitted infections) [40, 41]. Items include both binary (yes/no) and multiple response options. The World Health Organization Disability Assessment Schedule (WHO-DAS)-2.0 short form will assess functional impairment [42]. The WHO-DAS short form consists of 12-items measuring functional impairment across 5 domains: mobility, self-care, understanding and communication, life activities and societal participation. Items are scored on a 5-point Likert scale and summed to derive a total scale. Higher scores indicate worse functioning [40]. The EuroQual-5 Dimension (EQ-5D-3 L) will be used to calculate quality adjusted life years (QALYs) among youth for the cost-effectiveness analysis [43]. The EQ-5D-3 L is designed for describing and valuing health in terms of 5 dimensions: mobility, self-care, usual activities, pain/discomfort, and anxiety/depression [33]. Each dimension has 3 response categories rated as “no problems”, “some problems”, or “extreme problems”.

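### The youth noninferiority rule is written on the observed difference rather than its confidence limit, takes its 0.21 threshold from the power output, and conflicts with the no-difference null stated elsewhere

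*Protocol article*

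**What the plan says.** In the protocol article, the section on statistical power for student outcomes sets the error rates: "At a power of 0.8 and an alpha of *p* <.05 (one-tailed to assess noninferiority". It assumes clustering "using an ICC of 0.03 (based on prior ICCs for mental health outcomes of 0.01-0.04" and arrives at "the minimal detectable standardized effect size for a standardized difference (d) between the two of 0.21". The sentence then turns that figure into a decision rule: "in other words, at a negative difference of 0.21 or smaller, mobile supervision will be considered noninferior to standard".

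The same paragraph gives two detectable effects against the waitlist control: 0.26 for either YRI arm alone, and for both arms together "In a comparison of all 40 YRI schools as compared to the 10 control schools, the minimum detectable effect would be 0.21".

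Two other sections describe the mobile-versus-standard youth comparison differently. Hypothesis (b) under Study aims expects youth outcomes in the two supervision arms not to differ over time. The Quantitative analysis section plans to examine a null of no difference between the arms at post-intervention. Neither mentions a margin.

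The youth scales run in the unfavourable direction. The DERS is scored "with higher scores reflecting greater difficulties regulating emotions" and for the WHO-DAS "Higher scores indicate worse functioning". The article describes the HSCL in the same way.

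**The concern.** A noninferiority claim needs the confidence limit on the unfavourable side to exclude the margin. A rule on the estimate alone ignores sampling error: an arm whose true deficit is exactly the margin passes half the time.

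A margin should also express how much loss of benefit is acceptable. Here the article moves from what the sample can detect to what will count as noninferior with no step between, so the threshold reflects the number of schools and pupils.

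The section where an analyst would look for the correct test gives a null of no difference. A non-significant result against that null could reflect imprecision as easily as similarity.

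The youth result is what would support replacing in-person supervision with mobile supervision without loss for pupils. The article should therefore contain one valid statement of the test.

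**Working it through.** **Inputs (protocol article).** Power 0.80, one-sided alpha 0.05, ICC 0.03 (Statistical power analysis for student outcomes). 480 youth with mobile supervision, "480 youth from schools that will receive YRI delivered with standard supervision", 240 control youth, 24 youth per school (Settings and participants).

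**Step 1: reproduce the stated 0.21.** Minimal detectable effect = (z₀.₉₅ + z₀.₈₀) × √[DE × (1/n₁ + 1/n₂)], with DE = 1 + (m − 1) × ICC and SD = 1.

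- DE = 1 + 23 × 0.03 = 1.69
- z sum = 1.6449 + 0.8416 = 2.4865
- Mobile v standard: 2.4865 × √[1.69 × (1/480 + 1/480)] = 2.4865 × 0.0839 = 0.209, which rounds to 0.21
- One YRI arm v control: 2.4865 × √[1.69 × (1/480 + 1/240)] = 2.4865 × 0.1028 = 0.256, which rounds to 0.26
- Both YRI arms v control, same inputs: 2.4865 × √[1.69 × (1/960 + 1/240)] = 2.4865 × 0.0938 = 0.233, not 0.21. The stated pooled 0.21 appears with clusters of 12 and no attrition (DE = 1.33, giving 0.207).

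The 0.21 for mobile v standard is thus the output of a one-sided 5% test with 80% power at true equality.

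**Step 2: implied standard error.** SE = 0.21 / 2.4865 = 0.0845.

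**Step 3: chance of declaring noninferiority at a true deficit d.**

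- Literal clause: Φ[(0.21 − d)/SE]
- Confidence-limit rule: Φ[(0.21 − d)/SE − 1.645]

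| True deficit (SD) | Literal clause | One-sided 95% limit |
|---|---|---|
| 0 | 99% | 80% |
| 0.15 | 76% | 18% |
| 0.21 | 50% | 5% |
| 0.26 | 28% | 1% |

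Across standard errors of 0.074 to 0.090 (group clustering without attrition to school clustering with 20% attrition), the literal figure at 0.26 runs from 25% to 29%.

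**Step 4: observed deficit that may pass.** Literal clause: 0.21. Confidence-limit rule: 0.21 − 1.645 × 0.0845 = 0.071. At an observed deficit of 0.21, the one-sided 95% limit lies at 0.21 + 1.645 × 0.0845 = 0.349.

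**Step 5: the margin beside the control comparisons.** 0.21/0.21 = 100% of the stated pooled detectable effect; 0.21/0.26 = 81% of the single-arm one; 0.21/0.233 = 90% of the pooled one on matching inputs.

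**Step 6: cost of a formal superiority gate.** Suppose noninferiority could be claimed only if standard-supervision YRI also beats control.

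- SE for standard v control = 0.26/2.4865 = 0.1046.
- The shared standard arm contributes variance 0.0845²/2 = 0.00357, so the two test statistics correlate at −0.00357/(0.0845 × 0.1046) = −0.40.
- Power for superiority alone is 64% if the YRI effect is 0.21 and 80% if it is 0.26.
- From the bivariate normal, the chance of passing both at true equality is about 47% and 61%, against 80% for noninferiority alone.

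**The case against.** The strongest reply is that the sentence must be read whole. It names a one-tailed alpha of 0.05 for noninferiority, a rule on a point estimate has no alpha, and step 1 shows that 0.21 comes from a proper one-sided test. On that reading the disputed clause is a loose gloss and the error at the margin is 5%. This stands as an account of the likely intent. A reader might infer that the trial plans a 50% false-noninferiority rate; the article does not support that. The 50% is the risk if the clause were coded as written. The clause remains the only decision rule in the article, and the other two sections point to a different test.

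A reader might also infer that the margin equals the whole YRI effect the trial is sized for. It does not. The article gives detectable effects and no assumed or prior standardized YRI effect. The equality holds only for the pooled comparison, and that 0.21 does not follow from the inputs that give the other two figures. Against a single YRI arm the margin is 81%. A reason for the margin may also stand in a fuller document not shown here.

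Third, the article already plans superiority tests of each YRI arm against control. That is correct. They are not tied to reading the noninferiority result, but a formal tie is a design choice with a real cost in power.

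Finally, one could argue that the bound sits on the wrong side, because a negative mobile-minus-standard difference on these scales favours mobile. The article never defines the difference that way, and negative most naturally means mobile doing worse. This is a small ambiguity that stating the direction removes.

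**Conclusion.** Wrong as written, and moderate in weight because youth outcomes are secondary in this hybrid type 3 trial and the fidelity comparison is untouched.

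Two things are established. The article's one decision rule for youth noninferiority omits the confidence limit and takes its threshold from the minimal detectable effect. Its aims and analysis sections set a no-difference null for the same comparison, so no section states a complete and valid noninferiority test.

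The literal clause would accept an observed deficit about three times as large as the confidence-limit rule allows (0.21 against 0.07). These figures assume a normally distributed estimate and the standard error of 0.0845 implied by the stated 0.21.

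How much YRI benefit a result at the margin would preserve cannot be calculated from the article. What can be said is that the article does not show that any would be preserved.

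**What to change.** 1. Replace the clause with a rule of this form: mobile is noninferior on an outcome if the one-sided 95% confidence limit for the mobile-versus-standard difference, in the direction of mobile being worse (higher scores on DERS, HSCL and WHO-DAS), excludes a deficit of 0.21 SD.
2. Replace the no-difference null for youth outcomes in Study aims and Quantitative analysis with this hypothesis.
3. State openly that 0.21 is what the sample size supports, and report what share of the prior YRI effect it represents.
4. Report the already planned standard-versus-control comparison beside each noninferiority result. Where it shows no benefit, do not interpret noninferiority as retained YRI benefit.

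A formal superiority gate is optional, since it would lower the joint power to about 47–61%.

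The cost is wording only; no new data or arms are needed, and at manuscript submission youth recruitment had not begun. Noninferiority will be claimed less often than under the literal clause: 80% rather than 99% at true equality, which is the power the article already states. The fix keeps 0.21, so it makes the basis of the margin visible without making the margin stricter. As an illustration, a margin of 0.13 (half of 0.26) would leave 46–54% power with 480 youth per arm, depending on whether clustering is by school or by group.
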